### Hypothesis and objectives

We will robustly test our formal hypotheses yielding useful answers to the primary questions about the relative safety and efficacy of these novel forms of iron in iron-replete subjects. This study will address the major side effects of oral iron supplementation of iron-replete subjects. Specifically, we will compare the effects of two novel forms of iron and the widely used ferrous form on malaria (
*Plasmodium falciparum*) infectivity of host erythrocytes (assessed
*ex vivo*), bacterial proliferation (of selected species) in the presence of host plasma (assessed
*ex vivo*), redox stress and inflammatory stress (assessed
*in vivo*), gut irritation (assessed
*in vivo*), effects on the gut microbiome (assessed
*in vivo*). This set of indicators is referred to as the “safety profile”. Additionally, iron utilization (assessed
*in vivo*) will be compared to evaluate efficacy.

In Phase I, we will test the following research questions underpinning formal hypotheses using the design detailed below:

1. Does IHAT, a novel form of iron, produce beneficial and/or adverse effects comparable to FeSO
_4_ at equivalent iron doses?

IHAT and FeSO
_4_ administered at 60 mg Fe/day will produce comparable responses in malaria infectivity, bacterial proliferation, and iron status parameters. However, IHAT will produce less gut/systemic inflammation, and fewer effects on the microbiome.

2. Does Asprion, a novel form of iron, produce beneficial and/or adverse effects comparable to FeSO
_4_ at equivalent iron doses?

Aspiron and FeSO
_4_ administered at 60 mg Fe/day will produce comparable responses in malaria infectivity, bacterial proliferation, and iron status parameters. However, Aspiron will produce less gut/systemic inflammation, and fewer effects on the microbiome.

3. Are the adverse effects of FeSO
_4_ affected by co-administration of a multi-micronutrient powder (MNP)?

The safety profile of FeSO
_4_ for iron-replete individuals is not affected by its administration with a multiple micronutrient powder.

4. Are the beneficial and/or adverse effects of FeSO
_4 _comparable when administered daily or weekly?

The timing of FeSO
_4_ administration will not affect malaria infectivity, bacterial proliferation, and iron status parameters; however, weekly administration will produce less gut/ systemic inflammation and fewer effects on the microbiome.

In Phase II, we will test the following formal hypotheses using the design detailed below:

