### Study design

The Safe Iron Study is a double-blind, randomized, placebo-controlled study with iron supplementation in iron-replete older adults. For Phase I, adults are randomized to one of six intervention groups (
Table 1). For Phase II, adults are randomized to one of three intervention groups (
Table 2). For both phases, each arm undergoes an intervention period of 4 weeks, after which changes in parameters will be compared between baseline (week 0) and post-intervention (week 4) study visits.

**Table 1. T1:** Intervention groups for Phase I of the Safe Iron Study.

Subjects	Intervention Group	N	Intervention	Sampling
Fe-replete, PMW and men	Intervention 1	25	Placebo	0 and 4 weeks of intervention
	Intervention 2	25	FeSO _4_ (60 mg Fe/day)	0 and 4 weeks of intervention
	Intervention 3	25	FeSO _4_ (420 mg Fe/week)	0 and 4 weeks of intervention
	Intervention 4	25	FeSO _4_ (60 mg Fe/day) + MNP	0 and 4 weeks of intervention
	Intervention 5	25	IHAT (60 mg Fe/day)	0 and 4 weeks of intervention
	Intervention 6	25	Aspiron (60 mg Fe/day)	0 and 4 weeks of intervention

PMW, post-menopausal; FeSO
_4_, ferrous sulfate; MNP, multiple micronutrient powder; IHAT, iron hydroxide adipate tartrate

**Table 2. T2:** Intervention groups for Phase II of the Safe Iron Study.

Subjects	Intervention Group	N	Intervention	Sampling
Fe-replete, PMW and men	Intervention 1	25	FeSO _4_ (120 mg Fe/d)	0 and 4 weeks of intervention
	Intervention 2	25	IHAT (120 mg Fe/d)	0 and 4 weeks of intervention
	Intervention 3	25	Aspiron (120 mg Fe/d)	0 and 4 weeks of intervention

PMW, post-menopausal; FeSO
_4_, ferrous sulfate; IHAT, iron hydroxide adipate tartrate

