
### Interventions

This study will be using two novel forms of iron (IHAT and Aspiron) compared to FeSO
_4_. One arm will also include an MNP (MixMe™ Vitamin and Mineral Powder) donated by DSM Nutritional Products (Switzerland). The placebo will be comprised of Melojel® corn starch, donated by Ingredion (Manitoba, Canada). All forms of iron, MNP and corn starch have been approved for use in humans. This trial is only intended to evaluate the different supplement forms of iron on the structure or function of the body, not for a therapeutic purpose. All raw materials will be sent to the Richardson Centre for Functional Foods and Nutraceutical (RCCFN) at the University of Manitoba, Winnipeg, Manitoba, Canada for encapsulation. All interventions will be encapsulated into opaque, double zero capsules and appear identical in size, color and weight. The RCCFN is licensed as a Health Canada Natural Health Product Site with the ability to produce good manufacturing practices (GMP) and Hazard Analysis and Critical Control Points (HACCP) certified products. For the administration of capsules, each subject will receive a number-coded calendar-style monthly pill planner with a set number of capsules.

***Adherence.*** Adherence to supplement use will be assessed by using pill counts, a compliance calendar and iron status. Pill counts will be based on the number of pills remaining in the returned monthly pill planner. Subjects will be sent home with a compliance calendar to record their supplement intake and will be instructed to bring this document with them on the post-intervention study visit. Subjects will be instructed to return the number-coded calendar-style monthly pill planner with any unused sections or pills at the end of the 4-week study visit. The number of unused pills will be recorded at the 4-week study visit. Parameters of iron status will be measured in serum and will serve as additional measures of adherence to supplement protocol.

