## Methods: Assignment of interventions

### Randomization and blinding

The allocation sequence constructed using a block randomization with a block size of four. Random ordering of the allocations within each block was performed using for the study was performed using SFMT (SIMD-oriented Fast Mersenne Twister) algorithm (version 1.5.1) based randomization functions in the “StatsBase” Julia package. No stratification was used in the randomization, and the allocation sequence was implemented using the built-in “randomization” module in REDCap. This module references the provided allocation table and assigns participants based on order of enrollment.

For Phase I, subjects will be randomly assigned to one of the six treatment arms outlined in
Figure 1 at the time they enroll in the study. A randomization scheme for all entering subjects will be generated and stored by the Data Manager. The randomization sequence is known only to the Data Manager, and REDCap user roles were used to prohibit access to the allocation sequence until the participant was randomized to a treatment group. The unblinded key is maintained by the data manager and stored in a locked filing cabinet until the data collection for the study is complete. An active control group, using a corn starch placebo, will be used to provide a control for prospective changes over time and mimic any effects of ingesting a daily capsule in case it may be relevant. We will also provide placebo capsule to all other groups to blind against the FeSO
_4_ plus MNP group. All daily interventions groups will receive three physically similar capsules to ensure blinding of the treatments. The weekly intervention group will receive four physically similar capsules once per week.

For Phase II, subjects will be randomly assigned to one of the three treatment arms outlined in
Figure 2 at the time they enroll in the study. The randomization scheme will be the same as Phase I. We will not employ a control group in Phase II because any prospective changes over time or effects of ingesting a daily capsule will be determined from Phase I. All groups will receive four physically similar capsules to ensure blinding of the treatments.

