### Questionnaires

***Gut irritation questionnaire.*** This questionnaire
^34^ is designed to be self-administered but subjects will be given the opportunity to ask questions about how to fill out the questionnaire. This questionnaire is slightly modified from a validated questionnaire designed to address symptoms of gastrointestinal (GI) irritation after FeSO
_4_ supplementation
^34^. It will be completed at screening, baseline (week 0) and post-intervention study visits. Subjects will be given a copy of the questionnaire to take home. Subjects will be administered this questionnaire during weekly phone calls in which they will use to copy of the questionnaire to follow along with questions as they are asked over the telephone.

***Dietary assessment.*** Study subjects will receive a Food Amount Booklet and information about the 24-hour recalls at the baseline visit (Day 0). Three separate 24-hour recalls will be collected by phone during the 4-week study. Dietary intake data will be analyzed using Nutrition Data System for Research (NDSR) software version 2016, developed by the Nutrition Coordinating Center (NCC), University of Minnesota, Minneapolis, MN. Recalls will be collected using the multiple-pass 24-h recall method, assisted by the NDSR software and the goal for each participant will be to collect two weekdays and one weekend day of intake. Outcome data from NDSR will include daily estimated energy and nutrient intake, as well as food, food group, and dietary supplement data.

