## Conclusion

Overall, this double blind, placebo-controlled, randomized controlled trial will robustly test our formal hypotheses and yield useful answers to the primary questions regarding the safety and efficacy of these novel forms of iron supplements. The findings of this study will generate evidence to support development of a modality of providing bioavailable iron that does not or produces less adverse effects in iron-replete individuals. Ultimately, this study aims to contribute to the development of safe and effective forms of supplemental iron to address the global burden of iron deficiency and iron-deficiency anemia.

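### The capsule schedule identifies the weekly FeSO4 arm, so the unqualified double-blind claim does not hold for the weekly-versus-daily comparison, where self-reported gut irritation is the exposed outcome

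*Protocol article*

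**What the plan says.** **The claim.** Study design states: "The Safe Iron Study is a double-blind, randomized, placebo-controlled study with iron supplementation in iron-replete older adults". The Abstract says the same, and the Conclusion repeats it: "Overall, this double blind, placebo-controlled, randomized controlled trial". None of the three makes an exception for any arm.

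**The regimen.** Randomization and blinding states for Phase I: "All daily interventions groups will receive three physically similar capsules to ensure blinding of the treatments". The next sentence reads: "The weekly intervention group will receive four physically similar capsules once per week". The purpose given for the added placebo capsules is narrower than masking the schedule: "We will also provide placebo capsule to all other groups to blind against the FeSO", and the sentence goes on to name the FeSO4 plus micronutrient powder group. Rationale for the placebo control in Phase I says that the placebo group gets as many capsules as the other groups.

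**The packaging.** Under Interventions, "each subject will receive a number-coded calendar-style monthly pill planner with a set number of capsules". Subjects also keep a compliance calendar, and unused capsules are counted at week 4. Study timeline and visits has the assigned product given after breakfast at both study visits.

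**The outcome.** Hypothesis and objectives lists gut irritation in the safety profile. For question 4 it expects that "weekly administration will produce less gut/ systemic inflammation and fewer effects on the microbiome". The Questionnaires section describes a self-administered gut irritation form that is also used between visits: "Subjects will be administered this questionnaire during weekly phone calls". Statistical methods, item 4, tests gut irritation between groups.

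**The concern.** Capsules that look alike can hide which product is inside. They cannot hide how many are taken or how often. If only one arm follows a weekly schedule, anyone who sees the schedule and knows the list of arms knows the allocation.

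This matters most where the outcome depends on what a subject chooses to report. Daily and weekly FeSO4 are compared on the safety profile, which includes self-reported gut irritation. The section giving the rationale for the weekly arm cites earlier studies with fewer gastrointestinal complaints on weekly dosing. A published double-blind label on that comparison would claim protection against expectation effects that the described design does not give.

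Two routes reach beyond the questionnaire. Adherence is judged partly from capsule counts and the calendar, and Statistical methods uses nonadherence to decide who is left out of the assigned group. Termination of participation rests on the judgment of the study physician and the principal investigator. If the people making these decisions can recognise the weekly arm, the analysed set could differ by arm.

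**Working it through.** No power or sample-size figure is involved, and the plan states no figure to reproduce. The check is capsule arithmetic plus a reading of who can learn what.

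**Inputs.** Daily arms: three capsules, read here as three per day. Weekly arm: four capsules once per week (both from Randomization and blinding). Intervention: 4 weeks. Arms: six of 25, of which one is weekly (Table 1).

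**Capsule load.**

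| | Daily arms | Weekly arm |
|---|---|---|
| Per occasion | 3 | 4 |
| Per week | 3 × 7 = 21 | 4 × 1 = 4 |
| Over 4 weeks | 21 × 4 = 84 | 4 × 4 = 16 |

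The schedules differ in capsules per occasion, in frequency and in total. A calendar-style planner shows all three.

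**Subjects who can be identified.** Planned Phase I total: 6 × 25 = 150. Weekly arm: 25, or 25/150 = 1 in 6. Daily arms: 5 × 25 = 125.

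**Who can learn what.**

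- *Weekly subjects* see their own schedule. They can name their arm, and know they are not on placebo, if they have been told what the arms are. The consent form is not shown, so this is an assumption.
- *Daily subjects* can rule out the weekly arm and nothing more. Placebo, FeSO4, FeSO4 plus powder, IHAT and Aspiron all come as three similar capsules. Objectives 1 to 3 compare daily arms only, so their masking is intact.
- *Staff* who handle the planner, give the visit dose (three capsules or four) or count returns (out of 84 or out of 16) can recognise the weekly arm. The article does not say whether the telephone interviewers see any of this.
- *Laboratory staff* receive specimens identified by study code number (Data capture and management). Data access restricts each investigator to the relevant forms until unblinding.

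**Outcome by outcome for objective 4.** The three primary outcomes are malaria infectivity, bacterial proliferation and fecal calprotectin, all laboratory measures. The inflammation and microbiome outcomes named in the question 4 hypothesis are also measured in blood and stool. Gut irritation is the self-reported measure, and it is collected repeatedly while the subject follows the schedule.

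**Internal conflict.** The statement that the placebo group gets the same number of capsules as the other groups fits the daily arms (3 and 3) but not the weekly arm (21 against 4 per week).

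**The case against.** The strongest defence is that the article discloses the weekly regimen openly and attaches its statement about ensuring blinding only to the daily groups. The primary outcomes are laboratory-based and specimens are coded. The gut irritation questionnaire is not in the Outcomes section's list of primary or secondary outcomes. The article is condensed and Figure 1 is not shown. Most of this stands and limits the point to one self-reported measure in one of four Phase I objectives. It does not rescue the unqualified label: gut irritation is still in the safety profile and is formally tested, and the text that describes the capsules describes no masking of the schedule.

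Four stronger readings are tempting, and the documents do not support them.

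- *The comparison is open-label and all 50 subjects in it are unmasked.* Subjects on daily FeSO4 cannot tell it from the other four daily products. At most the 25 weekly subjects can know their arm.
- *The bias favours weekly dosing.* The stated expectation points that way. But a subject who knows that the capsules hold iron, in one 420 mg weekly dose, might report more symptoms. No passage fixes the direction.
- *Each recognised weekly allocation discloses part of a randomization block.* The article gives a block size of four for six arms, so the make-up of a block cannot be read from the text.
- *The laboratory outcomes are unprotected.* Coded specimens and restricted data access argue against this. What remains is the indirect route through adherence and withdrawal decisions.

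**Conclusion.** The point holds in limited form. As described, Phase I is double-blind among its five daily arms. For the weekly arm (25 of 150 planned subjects) the schedule is not masked, so the weekly-versus-daily contrast is partly unmasked on one side. Objectives 1 to 3 are unaffected.

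The practical exposure is the gut irritation questionnaire in objective 4, with possible secondary effects through adherence and withdrawal. The size and direction of any bias cannot be derived from the document. The laboratory primary outcomes are largely protected.

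This rests on three assumptions: that three capsules means three per day; that no masking of the schedule is described in the full protocol or in Figure 1, neither of which is shown; and, for subjects' own knowledge, that they were told what the arms are. The point about staff does not depend on the third. The correction is worth making because it changes what objective 4 may claim about tolerability.

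**What to change.** 1. State that Phase I is double-blind among the five daily arms and that the dosing schedule is not masked for the weekly arm. Carry this into the Abstract, Study design, the Conclusion and later publications.
2. State who remains blinded for objective 4, naming at least the laboratory assessors and the analyst. Say whether the telephone interviewers, and those who judge adherence and withdrawal, can see the regimen.
3. Reconcile Study design, Randomization and blinding, Rationale for the placebo control in Phase I, and the Conclusion on capsule numbers and on the extent of blinding.
4. Report the objective 4 gut-irritation comparison as not fully blinded and supportive only. Rest the objective 4 conclusions on the laboratory outcomes from coded specimens.

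The cost is wording and a weaker claim for one self-reported outcome in one comparison. No dose, schedule or sample size changes. By Study status, 159 subjects were enrolled by May 2019 and data collection was expected to finish in June 2019. The change therefore belongs in the text and the analysis and reporting plan, and should be recorded before the investigators are unblinded.

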### Withdrawal of subjects

Subject participation may be terminated should they no longer meet any of the study criteria cited above, or if they fail to comply with study requirements or if a reported adverse reaction occurs that is considered severe. Subjects are free to withdraw from participation at any time during the study by writing, calling or emailing the study PI. The decision to terminate a participant from the study will be based on the judgment of the study physician and the study PI. If a participant does not complete the entire study, their stipend will be prorated accordingly depending on where the participant is in the study prior to withdrawal. If a subject withdraws or is withdrawn from the study, any data or specimens collected before withdrawal will still be used in the study.

## Methods: Data collection, management and analysis

### Data collection methods

***Laboratory analyses.*** At baseline (week 0) and post-intervention (week 4), subjects will provide blood and stool samples as well as complete several questionnaires. Blood pressure and pulse rates as well as anthropometric measurements will also be taken.
Table 3 outlines the questionnaires, biological and chemical analyses conducted at each study visit. Details of the analyses are described below.

***Blood samples.*** Blood samples will be collected at baseline and post-intervention. Depending on the analyses, 12-hour fasted and 2-hour postprandial, post-supplementation blood samples will be collected (
Table 3) and the following parameters will be assessed: CBC/differential;
*P. falciparum* infectivity of erythrocytes will be determined
*ex vivo*
^22^; bacterial proliferation potential will be conducted
*ex vivo* on plasma
^23^; plasma cytokines and pro-inflammatory markers (Meso Scale Discovery, MSD);
*ex vivo* mitogen or antigen-induced cytokine production) commercial ELISAs, R&D Systems, Minneapolis, MN
^24,
25^); iron and unsaturated iron-binding capacity (AU400 clinical chemistry analyzer, Beckman Coulter, Inc., Brea, CA); serum ferritin (commercial human ferritin ELISA, Thermo Scientific, Frederick, MD); transferrin (immunoturbidimetric procedure using the AU400 clinical chemistry analyzer, Beckman Coulter); transferrin saturation (determined from the relationship of the iron to total iron-binding capacity); transferrin receptor (commercial ELISA, R&D Systems); serum NTBI (serum treated with
*tris*-carbonatocobalate(III) trihydrate to saturate non-liganded transferrin binding sites followed by precipitation of proteins and ultrafiltration. Iron in the ultrafiltrate will be determined by electrothermal atomic absorption spectrophotometry or mass spectrometry (MS); hepcidin (commercial competitive ELISA, Bachem Group, Torrance, CA
^26^); tryptophan and kynurenine (liquid chromatography (LC)/MS/MS
^27^; F2α-isoprostanes (in-line solid phase extraction prior to quantitative analysis by ultra-performance LC/MS/MS
^28^); reduced glutathione/oxidized glutathione (Hypercarb HPLC column and quantitative detected by LC/MS/MS
^29^).

***Stool samples.*** Subjects will be asked to provide a sample at baseline and post-intervention visits Subjects will receive stool sample collection kit at the enrollment visit to bring the samples to study visits. The stool sample in the collection container will be placed in a plastic bag, surrounded by frozen gel packs to keep it cool for up to 18 hours. Aliquots of homogenized stool will be created and the following parameters will be assessed: fecal immunochemical tests (FIT) (OC-Auto Micro 80 Analyzer); calprotectin (commercial ELISA, R&D Systems,
^30^); myeloperoxidase (commercial ELISA, R&D Systems); neopterin (competitive ELISA, ALPCO, Salem, NH); inflammatory cytokines (Meso Scale Discovery, MSD); alpha-1 antitrypsin (commercial ELISA, R&D Systems); short chain fatty acids (derivatized and analyzed by LC-MS
^31^); microbiome DNA sequencing (stool DNA extracted using the QIAamp DNA Stool Mini kit, Qiagen, Valencia, CA, and amplicons of the V4 region of the bacterial 16S ribosomal DNA will be generated using primers
^32^. Amplicons will be purified on Angencourt AMpure XP beads (Beckman Coulter, Brea, CA) before submission to the Tufts University Core Facility for 250 bp paired-end sequencing on an Illumina MiSeq. Marker-gene sequencing data will be processed using the Quantitative Insights Into Microbial Ecology (QIIME) package
^33^.

